**Table 1: Study Schedule**

## 6.2. Randomization and Blinding

Participants will be randomized in a 1:1 allocation to receive FES (active pattern) or FES (sham pattern). Block randomization will be computer-generated, and the samples will be stratified for sex, given the potential differences in response and tolerability in these groups. A biostatistician will generate the randomization schedule, to be administered by a research assistant who is not associated with the study and instructed not to divulge group assignments to the participants to allow for concealment.

Participants and most study staff will be blinded. Only the physical therapist will need to monitor the participant. Measures taken to prevent functional unblinding include sensory and non-patterned sham and delivering automated messages to both active and sham groups. We will also evaluate each participant's ability to discriminate what treatment they received after each session to assess blinding effectiveness.

We will randomize subjects to study arms (20 days active or 20 days sham) using a secure online randomization module on REDCap. The block size will be fixed, and study personnel will be blinded to the randomization block size. An independent assistant, external to the study, will manage the randomization of subjects. The subject number and treatment code will be assigned

after the subject details have been obtained. Based on this information, the independent assistant will assign a unique subject number and treatment code, which will dictate the treatment assignment for the subject. The patterns will be pre-programmed into the take-home device by the biomedical team.

An unblinded code sheet that matches these stimulation codes to the treatment arm will be kept by an external coordinator and will not be available to the study coordinator or research assistants. The unblinded code sheet will have the following information:

1. The initial identifier codes for all potential participants
2. Stimulation code: 6-digit numerical code for the stimulation session
3. Condition number: Numerical code for the condition
4. Condition name: Name of the condition

A copy of this code sheet with the condition name removed will be provided to the study coordinator and research assistants. These linked codes ensure that the study coordinator and research assistants are kept blinded to the type of treatment each participant will receive.

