### **12.4. Data Management Responsibilities**

The responsibilities designated to each member of the research team will be documented on the Delegation of Authority Form. The study coordinator and research assistants will be responsible for the informed consent process, review for eligibility, questionnaire administration, data entry, device administration, and e-CRF entries. The study coordinator will be responsible for AE/SAE documentation and reporting, while the investigator will be responsible for the AE assessment, review of the AE documentation forms, and overview of the research staff.

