### **14. Data Analysis**

#### **14.1. Sample Size Considerations and Study Feasibility**

For this pilot feasibility trial, we aim to recruit 20 participants in total.

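### The code sheet given to the coordinator and research assistants keeps the condition number, so the staff blind rests on a single shared A/B label

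*Protocol*

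**What the plan says.** Section 6.2 sets out a two-arm, 1:1 randomisation stratified by sex. An independent assistant outside the study manages it through a REDCap module and assigns the subject number and treatment code once subject details are in hand. On block size the protocol says: "The block size will be fixed, and study personnel will be blinded to the randomization block size".

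An external coordinator keeps the unblinded code sheet. Its first field is "The initial identifier codes for all potential participants", its second "Stimulation code: 6-digit numerical code for the stimulation session" and its third "Condition number: Numerical code for the condition". The fourth is the condition name. For the site staff, the protocol says: "A copy of this code sheet with the condition name removed will be provided to the study coordinator and research assistants". It concludes that the linked codes guarantee that these staff stay blinded to each participant's treatment.

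Section 12.4 makes the same coordinator and assistants "responsible for the informed consent process, review for eligibility, questionnaire administration, data entry, device administration". It also gives the coordinator the documentation of adverse events, as do Sections 9.2 and 11.2.2. Section 8.1 lists the number and nature of adverse events among the primary outcomes, and Hypothesis 1b in Section 4 compares their number between arms.

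**The concern.** Removing the name of the condition but keeping its number does not mask participants individually. It sorts them into two visible groups and hides only which group is which. The blind then depends on one binary fact that all participants share, and anything learned about one participant applies to all of them.

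The staff who hold this copy are not remote from the data. They enrol participants, administer devices and questionnaires and enter data, and the coordinator records adverse events. If they come to believe they know the labelling, it could affect how adverse events are elicited and recorded, and how participants are supported through a daily schedule in which dropout and compliance are also primary outcomes. Because the sheet covers potential as well as enrolled participants, unused rows carry a condition number too, which raises a further question about concealment of later allocations.

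**Working it through.** **What the staff copy contains.** The plan gives no figure to reproduce here; the check is a count of what the sheet reveals.

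| Field | Full sheet | Staff copy |
|---|---|---|
| Identifier, all potential participants | yes | yes |
| Stimulation code | yes | yes |
| Condition number | yes | yes |
| Condition name | yes | removed |

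**Inputs.** Two arms (Section 6.2); target of 20 participants (Section 14.1: "For this pilot feasibility trial, we aim to recruit 20 participants in total"). One condition number per arm is an assumption. It is the plain meaning of the field description, but the protocol does not rule out several numbers per arm.

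**One certain identification.** With two numbers and two arms, knowing the arm behind one number fixes the other. Participants labelled: 20 of 20. With participant-unique codes, one identification directly labels 1 of 20.

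**Uncertain guesses.** The shared number also lets weak impressions be pooled. Let q be the assumed probability that a guess about one participant's arm is right, with guesses independent. Each guess is a vote on the labelling. After k participants, the majority is right with probability

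P = Σ over j > k/2 of C(k, j) q^j (1 − q)^(k − j), plus half the probability of a tie when k is even.

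For q = 0.70 and k = 5: 10 × 0.343 × 0.09 + 5 × 0.2401 × 0.30 + 0.16807 = 0.309 + 0.360 + 0.168 = 0.837.

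| Assumed q | k = 1 | k = 5 | k = 10 | k = 20 |
|---|---|---|---|---|
| 0.60 | 0.60 | 0.68 | 0.73 | 0.81 |
| 0.70 | 0.70 | 0.84 | 0.90 | 0.97 |
| 0.80 | 0.80 | 0.94 | 0.98 | 0.998 |

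Without a shared number there is nothing to pool on, and each participant's arm stays guessable only at the individual rate q.

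**Where a guess could come from.** Section 7.1 gives active stimulation at 1–25 mA to activate muscles; Section 7.2 gives sham at 1–8 mA, sensory only and in a different pattern. Section 6.3 has participants note their intensities on the four channels, and sessions are held by video and recorded. An intensity above 8 mA lies outside the stated sham range. These are possible cues; the protocol gives no rate at which they would succeed.

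**Upcoming allocations.** Unused rows are labelled along with used ones. Predicting the next named participant's arm needs one more fact: which row that person will receive. Section 6.2 does not say whether rows are in schedule order, whether identifiers are used in sequence, or when the staff copy is handed over.

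Nor is the comparison without the condition number a flat 50%. If the first allocation in a block of size b is known, the next one in the same stratum and block is the opposite arm with probability (b/2)/(b − 1). For assumed block sizes 2, 4, 6 and 10 that is 1.00, 0.67, 0.60 and 0.56. The protocol does not state the block size.

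**The case against.** The best case for the plan is that other controls stand around the sheet.

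- **Assignment.** A person outside the study assigns subject numbers through REDCap, within sex strata, after subject details are obtained. A reader might infer that concealment fails for every later participant and that the block pattern can be read off. The documents do not support that, because both need a row order that is nowhere stated. This part of the objection stands.
- **Outcome rating.** A reader might also infer that the depression ratings are compromised. Section 6.4 has the clinical scales scored by a blinded rater with no other role in the trial, who is not named as receiving the sheet. It also provides for documenting a broken blind and seeking a substitute. The other efficacy scales are self-reported through REDCap. This part stands as well.
- **Visibility on video.** It is tempting to say that staff can simply see who is on active treatment. Section 6.3 requires a voluntary Duchenne smile whenever stimulation is on, under a mask open only around the eyes and mouth, and Section 6.2 sends automated messages to both arms. Section 6.2 names the physical therapist as monitoring the participant and Section 11.1.3 has an investigator hold the sessions; neither is named as holding the sheet. A certain identification from video is therefore unproven. But the weakness does not need certainty, and Section 12.4 gives device administration to the staff who do hold it.
- **Blinding will be measured.** The index in Section 14.2 assesses patients' blinding, and the check in Section 6.2 asks participants. Neither would show that staff had decoded the sheet.

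The objection narrows the consequences. It does not justify keeping an arm-level number on the staff copy: the devices are pre-programmed by the biomedical team, and no task the protocol gives these staff needs it.

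**Conclusion.** The point holds in a limited form. On the assumption of one condition number per arm, the staff copy is grouped A/B labelling, and the statement that the codes guarantee staff blinding is not correct. One correct identification labels 20 of 20 participants instead of 1 of 20. Pooled guesses at an assumed 60–80% accuracy label the sheet correctly with probability 0.68–0.94 after 5 participants and 0.73–0.98 after 10. Those accuracies, and the independence of the guesses, are assumptions.

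The direct exposure is in enrolment, device and questionnaire administration, and the coordinator's adverse-event documentation, the last of which bears on a primary outcome. Concealment can be weakened but is not shown to fail, and the HAM-D-17 rater is not directly exposed. For a 20-participant feasibility pilot, this should be fixed before enrolment because exposure cannot be reversed, but it does not invalidate the design.

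**What to change.** In Section 6.2, remove the condition number as well as the condition name from any copy held by the coordinator or research assistants, or replace it with a code unique to each participant. Any stimulation code left on that copy should likewise not be shared across an arm. Release each participant's row only after assignment. Keep the full list with the external coordinator and the biomedical team that programs the devices, and reword the sentence on linked codes to match.

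The cost is a wording change and a re-issued code list, with no burden on participants. Varying the block size is a separate design preference and is not needed to close this gap.

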### **6.3. Study Schedule**

It is important to note that consent, scales, and experiments will all take place in a private room. Any phone calls will take place in a private lab environment as well.

#### **Screening Visit**

Individuals who are referred by a mental health care provider will be contacted via phone for a pre-screening call to give them additional background information on the study and associated participant responsibilities. Researchers will keep a Telephone Contact log (within the Master Linking Log) for each telephone conversation with a participant throughout the study. There will be an entry for each participant, and the log will be filed in the participant binder. If a participant is determined to be ineligible, data from the screening will be retained.

During the telephone pre-screening, researchers will provide a brief background about MDD and FES. Any initial questions will be answered at this point. The timeline of visits will then be explained; there will be a screening visit which takes place over the phone, and 3 on-site Visits, including 1 mask development visit, 1 mask delivery visit, and 1 very last follow-up visit. The participant will be informed that compensation for their participation will be received at each on-site Visit throughout the study. The participant will be asked if they have any additional questions. Once all questions have been answered, the participant will be asked if he/she is still interested in participating in the study. If yes, the researcher will obtain verbal consent and ask them to confirm their email address. They will access a screening survey through REDCap via a link which will be sent to their email. The survey will be a preliminary measure of their eligibility for the study.

Once a participant has completed the REDCap screening form, participants who appear eligible will receive another telephone call to schedule the screening visit for them.. The written informed consent will be obtained at the first on-site visit.

The following procedures will be completed at the screening visit over the phone:

- Inclusion/exclusion review
- Demographic review
- Review of medical, psychiatric, and medication history, including review and confirmation of diagnosis
- FES safety questionnaire

Additionally, female participants will be asked to confirm they are not pregnant and they are not planning to become pregnant throughout the duration of the study. If the subject satisfies the inclusion criteria, the mask development Visit, mask delivery Visit and baseline Visit (Visit 0) will be scheduled, and a reminder call or e-mail will be given at least 24 hours before each Visit.

### Mask Development Visit

The manufacturing of the mask will need to be personalized so that we can properly target the muscles for electrical stimulation. An accurate 3D scanning of the users' faces is a preliminary step to obtain the face configuration of each person to be able to customize the masks. We will propose the use of an effective and convenient 3D scanning technique based on photogrammetry in which several pictures of a user's face can be easily taken by digital cameras. Then, the pictures will be processed by an image processing technology to obtain the 3D profile of the face to be used for 3D printing of the mask mold. In order to collect the pictures of the subject's face, each subject will be invited to the photo shooting room, and, prior to attending the room, they will be asked to take off any object that may cause issues with capturing clear photos of their face (such as headbands, jewelry, reflecting make-ups, and long facial hair covering the cheek etc.).

After subjects have been informed and approved based on the FES safety questionnaire during the Screening Visit, single-use commercially available FES electrodes (MyndTec) made of skin-safe self-adhesive hydrogel and conductive carbon will be placed on the face, and a pilot FES trial will be carried out with a commercially available FES stimulator to stimulate their orbicularis oculi muscle and zygomaticus major muscle. In order to gather the proper electrode placement locations to induce the desired facial expression, 8 electrodes will be placed on the face: 2 electrodes under the left eye, 2 electrodes under the right eye, 2 electrodes on the left cheek, and 2 electrodes on the right cheek. The exact locations of these electrodes might differ based on the induced muscular response. The final placement will induce proper contraction with minimal FES current and minimal reported discomfort. The entire process approximately takes 20-30 minutes. Once the electrode locations are optimized, a picture will be taken so that the electrode placement will be adjusted accordingly on the personalized mask.

The subject will be seated on a chair with suitable lighting environment. A soft box lighting setup with adjustable position and lighting features will be used to achieve high resolution and minimize

image noise, as conventionally used in portrait photography studios. For each person, an average of 50 pictures will be taken covering mainly the face and head areas from left to right and down to up. The subject might be asked to put on a rubber hair cap during the photo shooting, which might lead to better results when converting the 2D photos into a 3D model during the image processing stage. The whole Mask Development Visit may approximately take 40minutes, and the subject will be able to leave the hospital once the FES pilot test and photo shooting is done. The photos will then be transferred to a computer to perform photogrammetric processing and generate the 3D spatial data of the subject's face. The 3D scanned mesh results will then be processed by means of Computer-Aided Design (CAD) software packages to modify the geometry and remove undesired areas, add required features for integrating electrodes, cabling, and fasteners, and finally export the CAD file to a 3D printable format. Then a rigid plastic model of the patient's face is 3D printed to be used as the mold to cast the personalized flexible mask made of food grade, skin-safe platinum cured silicone rubber.

#### Mask Delivery Visit:

The mold-printing and mask-making procedure will take 10-15 hours. We will use standard 3D printing technologies to print the designed mold geometry. After 3D printing the rigid plastic mold, we will cast the flexible mask with slots for affixing the electrodes to the desired locations of the mask surface facing the skin, and then run the cables for connection to the stimulation system through slits on the flexible mask. The mask will also be equipped with at least two hook-and-loop elastic band and Velcro fasteners passing around the back of the head to hold the mask on the face during the stimulation period. The mask will have a flexible nose wire extracted from commercially available surgical masks to better fit the mask around the subject's nose. The mask customized for the subject will then be ready for mounting on the subject's face to perform the targeted stimulation. We will deliver the customized mask during an on-site visit to the user with instructions about how to put the mask on and apply the stimulation.

Due to the customized design for each person with all components integrated into it, we expect that the process of wearing the mask and using it would be very straightforward. The instructions of use will be provided to the participants in both written and verbal formats. The participant will turn on the unit. There will be an external box with four switches for the four channels. The switches control the stimulation in the set-up phase. They will be in the set-up position at the start. Once all 4 channels are adjusted, the participant can switch all of the channels to the ready position to start the stimulation for the session. They should note down their suggested stimulation intensities for the 4 channels. A test of FES with mask will be done in this visit to walk the participant through the procedure and answer all the questions. Participants will receive the mask preprogrammed stimulator, and webcam at the end of this Visit.

#### Baseline Visit (Visit 0)

A baseline assessment will take place before the first FES visit. The research team will assess depression, sleep, and quality of life via videoconference appointments at baseline.

The remainder of the activities will be planned according to schedule, resources, timing, and subject tolerability. A baseline assessment may happen on the first day of stimulation prior to the FES (e.g., a questionnaire). The baseline visit includes:

- Psychiatric interview
  - Hamilton Depression Rating Scale 17-Item (HAM-D-17)
- Self-report scales (this information will be recorded in REDCap)
  - 16-Item Quick Inventory of Depression Symptomatology (QIDS-SR-16)
  - Generalized Anxiety Disorder-7 Scale (GAD-7)
  - World Health Organization-5 Well-Being Index (WHO-5)
  - Pittsburgh Sleep Quality Index (PSQI)
- Assessment of CONMED record
- Assessment of FES Expectancy

### FES Visits (20 Visits)

The FES study visits will be conducted at home with personalized masks and a programmable stimulator. Participants will be randomized to undergo either 20 days (weekdays) of FES once a day (20 visits) or 20 days of sham FES once a day (20 visits). Participants will be allowed to miss up to 2 treatment visits. Additional visits will be added on to reach the expected number of visits if it is within a reasonable timeframe as determined by the investigator.

The FES treatment sessions will be 60 minutes in duration (15 min for preparations and 45 min for the stimulation), delivered 5 times/week, for a total of 20 FES sessions. Each FES session will take place over a videoconference. The webcam will be used to record facial expressions during the study because the activation of particular muscles may later need to be confirmed and analyzed. The video recordings are mandatory, and participants' smiles will be detectable through the hollowed-out area around the eyes and the mouth, but only to be viewed by the study personnel for quality assurance purposes. Whenever the FES is on, participants will be required to voluntarily produce the Duchenne smile. Automated messages to voluntarily “smile & hold” (over speakers) precisely timed with the FES-related facial stimulations (only during 15 sec ON times) will be delivered.

Each visit (15 min preparations and 45 min stimulation) will consist of the following:

- A review of FES side effects and adverse events will be completed daily before and after stimulation.
- The users only need to place the mask on their faces and follow the instructions they received at the mask delivery Visit.
- 45 min of FES stimulation to target Duchenne muscles.
- Participant tolerance

- Subjects will be queried each day about their experience and how they are doing. If participants or their family members express that the participant is having difficulty, the study staff will work with them to reduce any possible burden.
- A participant “FES Experience” Assessment will be completed with the subject at the end of each week (Visits 5, 10, 15, and 20) via videoconference to monitor the participant burden.
- Psychiatric interview - will be completed with the subject at the end of each intervention week via videoconference appointment during the 20 days (sessions 5, 10, 15, 20).
  - Hamilton Depression Rating Scale 17-Item (HAM-D-17)
- Self-report scales - will be completed by the subject daily after treatment using REDCap:
  - 16-Item Quick Inventory of Depression Symptomatology (QIDS-SR-16)
- Self-report scales - will be completed with the subject at sessions 5, 10, 15, and 20 using REDCap:
  - Generalized Anxiety Disorder-7 Scale (GAD-7)
  - World Health Organization-5 Well-Being Index (WHO-5)
  - Pittsburgh Sleep Quality Index (PSQI)
- Assessment of CONMED record - will be completed with the subject at sessions 5, 10, 15, and 20 via videoconference appointment.
- Assessment of FES Expectancy - will be completed with the subject at sessions 5, 10, 15, and 20 using REDCap.

